###### Metabolome

The relative intensity of fecal metabolites was assessed in the polar, semipolar, and nonpolar fractions of fecal samples using untargeted metabolite profiling (metabolomics).

Fecal samples were freeze-dried under vacuum and extracted using a previously described method [66] with minor modifications. Briefly, 50 mg of lyophilized fecal samples were homogenized with a ceramic bead for 1 minute, and then 400 µL of 75% methanol/Milli-Q water were added. The tubes were vortexed for 30 seconds, sonicated for 2 minutes, and transferred into ice for 10 minutes. Afterward, 1 mL of methyl tert-butyl ether was added, and the mixture was incubated for 1 hour at 450 revolutions per minute. Then, 550 µL of Milli-Q water were added, and after 10 minutes of incubation, the mixture was centrifugated at 14,000 × g for 25 minutes to separate the aqueous (lower) and organic (upper) phases. The polar and lipid extracts were evaporated under a stream of nitrogen at room temperature. The dried samples were stored at –80 °C until LCMS analysis. The metabolite profiling analyses were carried out using high-resolution LCMS on a Shimadzu 9030 quadrupole time-of-flight mass spectrometer equipped with electrospray [67]. An aliquot of the polar extract was taken and analyzed using hydrophilic interaction liquid chromatography [67], and semipolar metabolites were resolved using reverse-phase chromatography [68]. The organic phase was analyzed using the lipidomic methodology [69].

###### Targeted Metabolites

Aliquots of 1 g of fecal samples were sent to Plant & Food Research, New Zealand, for organic acid (including short-chain fatty acids) measurement using an LCMS method. In total, 14 linear and branched organic acids (carbon-1 to carbon-6) were derivatized with a probe using mass spectrometry (MS) probe and stable isotope techniques as previously described [70] with modifications ([name], unpublished data, September 2017) and measured using targeted LCMS on a SCIEX LCMS/MS QTRAP 5500 instrument equipped with a Turbo V ion source and atmospheric pressure chemical ionization probe coupled to an ExionLC ultra–high-pressure liquid chromatography (HPLC) system (Shimadzu). Labeled internal standards for each organic acid were used to ensure accurate quantification [71]. Textbox 1 provides the names and corresponding acronyms of the organic acids analyzed.

Plasma and fecal organic acids analyzed using liquid chromatography mass spectrometry with the corresponding acronym.
**Full name and acronym**
Formic acid: FALactic acid: LAAcetic acid: AAPropanoic acid: PAIsobutyric acid (2-methylpropanoic acid): IBAButyric acid (butanoic acid): BASuccinic acid: SucA2-methylbutyric acid (2-methylbutanoic acid): 2MBAIsovaleric acid (3-methylbutanoic acid): IVAValeric acid (pentanoic acid): VA3-methylvaleric acid: 3MVA4-methylvaleric acid (isocaproic acid): 4MVACaproic acid: CAHexanoic acid: HA

Extraction methods for bile acid analysis followed those outlined elsewhere [72]. Briefly, 50 mg of wet fecal samples were extracted with 100 µL ice-cold methanol containing internal standards (10,000 nM of deuterium labelled cholic acid and deuterium labelled chenodeoxycholic acid). The mixture was homogenized for 30 seconds, incubated at –4 °C for 30 minutes, and centrifuged at 18,000 × g for 20 minutes. Then, 20 µL of the supernatant were dissolved in 80 µL of 0.1% aqueous formic acid solution, vortexed, and proceeded to HPLC for analysis. This analysis was carried out using high-resolution LCMS on a SCIEX LCMS/MS QTRAP 6500+ system coupled to an ExionLC system [73]. Textbox 2 provides the names and corresponding acronyms of the bile acids analyzed.

Fecal bile acids analyzed using liquid chromatography mass spectrometry with the corresponding acronym.
**Full name and acronym**
β-muricholic acid: βMCACholic acid: CAChenodeoxycholic acid: CDCADeoxycholic acid: DCAGlycocholic acid: GCAGlycohyodeoxycholic acid: GHDCAGlycoursodeoxycholic acid: GUDCAGlycolithocholic acid: GLCAHyocholic acid: HCAHyodeoxycholic acid: HDCAIsolithocholic acid: ILALithocholic acid: LCATaurine: TaurineTauro-β-muricholic acid: TβMCATauro-α-muricholic acid: TαMCATaurocholic acid: TCATaurochenodeoxycholic acid: TCDCATaurodeoxycholic acid: TDCATauroursodeoxycholic acid: TUDCAUrsodeoxycholic acid: UDCA

##### Blood Samples

###### Overview

In total, 2 research team members trained in phlebotomy collected peripheral blood at each clinic visit. At both screening and follow-up clinic visits, 1 aliquot (6 mL) of a blood sample was taken into a lithium-heparin vacutainer tube to measure fasting blood glucose, lipid panel (total cholesterol, low-density lipoprotein [LDL] cholesterol, high-density lipoprotein [HDL] cholesterol, and triglycerides), C-reactive protein, and liver function, enzymes, or general health markers, and 1 aliquot (4 mL) of blood was taken into an ethylenediaminetetraacetic acid tube (Becton, Dickinson and Company) for a complete blood count. Before and following each intervention phase, 1 aliquot (6 mL) of a blood sample was taken into a lithium-heparin vacutainer tube (Becton, Dickinson and Company) to analyze the complete lipid profile. The collected blood samples were kept at room temperature and delivered to Canterbury Health Laboratories (Christchurch, New Zealand) for analysis within 1 hour of collection.

At all time points except for the screening clinic visits, an additional 6 mL of blood were collected into 1 × 6-mL lithium-heparin vacutainer tubes to assess plasma metabolome and known metabolites (bile acids and organic acids). The 6-mL vacutainer was kept on ice and processed within 1 hour. The tubes were centrifuged at 4 °C for 5 minutes at 2000 × g, with high acceleration and slowest deceleration to separate plasma from cells. Plasma samples were distributed into 500-µL aliquots and stored at –80 °C until further analysis.

###### Metabolome

Polar metabolites were extracted using a single-phase extraction [68]. Briefly, 50 µL of plasma were extracted using 450 µL of prechilled acetonitrile:water (9:1 v/v). The mixture was shaken for 60 seconds and then centrifuged at 14,000 × g and 4 °C for 10 minutes, and then the extract was placed into an HPLC vial for analysis. Plasma semipolar metabolite extraction was conducted as described previously [74]. Plasma semipolar metabolite extraction was performed by adding 400 µL of ice chloroform to methanol in a 1 to 1 part volume to volume ratio to 50-µL plasma samples, vortexing it for 30 seconds, and incubating it for 1 hour at –20 °C. Then, 200 µL of Milli-Q water were added to the mixture, vortexed, and centrifuged at 14,000 × g and 4 °C for 10 minutes. The supernatants were evaporated to dryness under a stream of nitrogen and stored at –80 °C until analysis. On the day of the analysis, the semipolar extracts were thawed at room temperature (18 °C, –2 °C to +2 °C) and redissolved in redissolved in acetonitrile to water in a 1 to 9 part volume to volume ratio. The mixture was vortexed for 1 minute and then centrifuged (14,000 × g at 4 °C for 10 minutes). The extract was then transferred into an HPLC vial for analysis. Lipid extraction was performed by placing 10 µL of plasma into an Eppendorf tube, adding 95 µL of butanol to methanol in a 1 to 1 part volume to volume ratio, and then spiking it with 5 µL of internal standard SPLASH mix (Avanti Polar Lipids, Merck KGaA) [69]. The mixture was then vortexed for 1 minute, sonicated at room temperature for 60 minutes, and centrifuged at 14,000 × g for 10 minutes at 20 °C. The extract was then transferred to an HPLC vial and stored at –80 °C until LCMS analysis. The plasma polar, semipolar, and nonpolar extracts were analyzed using the LCMS methods for the plasma samples [69].

###### Targeted Metabolites

Textbox 1 shows the names and corresponding acronyms of the organic acids analyzed. Aliquots of 200 μL of heparin plasma were sent to Plant & Food Research, New Zealand, for analysis of organic acids via LCMS. A total of 14 linear and branched organic acids (carbon-1 to carbon-6) were derivatized with a probe using MS probe and stable isotope techniques as previously described [70] with modifications ([name], unpublished data, September 2017) and measured using targeted LCMS on a SCIEX LCMS/MS QTRAP 7500 instrument equipped with a Turbo V ion source and atmospheric pressure chemical ionization probe coupled to a Nexera ultra-HPLC system (Shimadzu). Labeled internal standards for each organic acid were used to ensure accurate quantitation [71].

#### Clinical Measurements

##### Anthropometry

Height, weight, BMI, and waist circumference were measured at each visit (ie, screening, baseline, postintervention assessment, and follow-up) according to the procedures established by the New Zealand Ministry of Health protocols for collecting height, weight, and waist measurements [75].

Standing height was measured to the nearest 0.1 cm using a calibrated stadiometer. Body weight was measured to the nearest 0.1 kg using calibrated body weight scales. Both measurements were taken with participants removing heavy outer clothing and shoes. Waist circumference was taken over clothing, and hence, the level of the measurement was determined by the participant to identify their waist. This measurement was taken to the nearest 0.1 cm using a calibrated measuring tape. All measurements were conducted twice, with a third reading when the 2 readings varied by >0.5 units. BMI was calculated as weight (in kilograms) divided by height (in meters squared).

##### Blood Pressure

Blood pressure was also measured at each morning clinic visit (ie, during screening, at each phase of baseline, at the postintervention assessment, and at follow-up) according to the recommendations established by the Australian expert consensus [76]. The measurement was taken using a validated, automated blood pressure monitor with a fitted-sized upper arm cuff. Participants were seated at rest for 5 minutes with feet flat on the floor, legs uncrossed, back and arm supported in a relaxed position, and the cuff at heart level. Measurements were taken on their nondominant arm. The blood pressure readings were then recorded immediately and compared with those recorded in previous clinic visits. When a high blood pressure value reading was noted, participants were asked about any unusual incidents that may affect the readings. These were then recorded on the eCRF of the participant.

##### Lipid Profile

As mentioned previously, the full lipid profile was measured at each morning clinic visit (ie, during screening, at each phase of baseline, at the postintervention assessment, and at follow-up) according to the recommendations of the Canterbury Health Laboratories (Christchurch, New Zealand). The lipid profile consisted of 5 components: total cholesterol, LDL, HDL, triglycerides, and TC/HDL ratio. Total cholesterol measures overall cholesterol level; LDL is a fat that circulates in the blood, moving cholesterol around the body where it is needed for cell repair and depositing it inside artery walls. HDL, also known as “good cholesterol,” helps remove cholesterol from the bloodstream. Triglycerides represents the main lipid component of dietary fat. The TC/HDL ratio, a sensitive predictor of heart disease [77], was also calculated.

#### Patient-Reported Outcomes

##### Daily Bowel Movement and Daily Bread Diary

Upon enrollment and throughout the study, participants were asked to complete a daily bowel movement and bread diary via an app. This app was developed by one of our research team members ([name] from AgResearch, New Zealand) using a REDCap application programming interface token. The token is a unique code that is associated with a single user on a specific REDCap project, which allows the user to programmatically access data within the project. Upon installing the app by the participants, the app downloaded the diary questions from REDCap, linking the app (on that phone) to the corresponding participant’s allocated unique identifier at the point of consent to the study. All submissions were then recorded under the corresponding participant identifier. The submissions were stored on the app and submitted to REDCap with each entry. To ensure data integrity, the app “talks to” REDCap to retrieve the most recent record for the participant and increment accordingly, preventing any answers from being overwritten.

Each diary took approximately 2 minutes to complete each time. The bowel movement diary provided a comprehensive record of the bowel habits of the participants and assessed the following variables: (1) frequency of bowel motions, which included questions on spontaneity and completeness of bowel movement; (2) ease of defecation or level of straining; (3) fecal form based on the Bristol stool scale; (4) menstruation (if applicable); and (5) presence of blue dye (if applicable, see the following sections for further details).

The daily bread diary assessed compliance with the consumption of intervention bread and general bread consumption preferences. Consumption of bread slices and days consumed for each participant were determined through the following equations:

Compliance regarding bread slices consumed = ([number of bread slices consumed / number of bread slices expected to be consumed] × 100%)

Compliance regarding days consumed = ([number of days consumed / number of days expected to be consumed] × 100%)

Compliance with the intervention (bread slices and days consumed) was determined by calculating the mean percentage compliance for each bread and the proportion of participants meeting >50% compliance.

This bread diary also determined (1) whether the DRB-fortified and placebo breads were toasted; (2) minutes of toasting (if applicable); (3) additional commercial sliced bread consumed (if applicable, during the washout period); and (4) the type, brand, and amount of additional bread consumed (if applicable).

##### Web-Based Questionnaires

###### Overview

One day before each phase of baseline, postintervention, and follow-up clinic visits, participants received an individualized email with a link to 6 web-based questionnaires. These web-based questionnaires, which were emailed to participants, were similarly administered via the REDCap system. All these questionnaires took approximately 15 minutes to complete each time.

###### Gastrointestinal Symptom Rating Scale

The Gastrointestinal Symptom Rating Scale, a validated instrument that assesses gut comfort, was administered before and during the intake of intervention and placebo bread. The Gastrointestinal Symptom Rating Scale has a 1-week recall that assesses symptom severity using a 7-point Likert scale ranging from “no discomfort at all” to “very severe discomfort.” The complete instrument consists of 15 primary items clustered into 5 domains: diarrhea, constipation, reflux, abdominal pain, and indigestion [78-80].

###### Patient-Reported Outcome Measurement Information System: Anxiety and Depression

This consists of a validated system with multiple domains, where specific domains can be chosen to be integrated into diverse data collection tools. This chosen questionnaire evaluates anxiety and depression in the last 7 days in detail as well as mental symptoms rated by severity from “not at all” to “very much” and from “never” to “always” [81,82].

###### World Health Organization 5-Question Well-Being Index

This is a short self-reported rating scale of current well-being. It consists of 5 statements concerning the previous 2 weeks adjusted to 1 week (*all of the time*=5; *most of the time*=4; *more than half of the time*=3; *less than half of the time*=2; *some of the time*=1; *at no time*=0) [83].

###### Warwick-Edinburgh Mental Wellbeing Scale

A 14-item scale adjusted to 1 week was used to explore mental health and well-being over the previous 2 weeks. The Warwick-Edinburgh Mental Wellbeing Scale has 5 response categories summed to provide a single score. The items are all worded positively and cover both feeling and functioning aspects of mental well-being. This questionnaire covers key aspects of psychological functioning—optimism, autonomy, agency, curiosity, clarity of thought, and positive relationships—and positive affect (feelings)—confidence, feeling relaxed and cheerful, and having energy to spare (*none of the time*, *rarely*, *some of the time*, *often*, and *all of the time*) [84].

###### Multidimensional Fatigue Symptom Inventory–Short Form

This is a 20-item self-report instrument with a 7-point scale that indicates to what extent each statement applies to the participant, ranging from “yes, that is true” to “no, that is not true,” designed to measure fatigue. It covers the following dimensions: general fatigue, physical fatigue, mental fatigue, reduced motivation, and reduced activity [85].

###### Subjective Vitality Scale

A 6-statement instrument assesses the state of feeling alive and alert (ie, having energy available to oneself). The statements explore the current feeling on a scale of 1 to 7 (1=*not at all true*, 4=*somewhat true*, and 7=*very true*) [86].

#### Dietary Intake

Paper copies of a nonconsecutive 3-day food diary were posted to all enrolled participants to complete before each of the 5 study visits (ie, at baseline, postintervention assessment, and follow-up). All enrolled participants were provided with verbal and written instructions by the study dietitian on completing a food diary. The written information included instructions on how to describe food using household measures. The food diary included written prompts for detailed information about when and where the food was consumed and who they were with when the food was consumed; the type of food or drink; brand details; preparation or cooking methods; and quantity, as well as a section for recipe details. Participants were also asked to record any reasons why their intake may have differed from their normal eating routines. Before each subsequent appointment, participants received reminder emails to start the food diary and the same written information on completing the food diary. Participants could contact the study dietitian if they required further guidance on completing the food diary. At each clinic visit, the study dietitian reviewed each food diary to ensure that adequate detail was provided and check whether additional foods and beverages were consumed but not recorded. In total, 2 nutrition graduates trained in dietary assessment entered the food diaries into a dietary analysis software, Foodworks Online Professional (version 1.0; Xyris Software) [87]. The New Zealand Food Composition Database (FOODfiles 2018; version 1.0) was used to estimate energy and nutrient intakes. After the primary outcome was analyzed and the study was unblinded to the intervention, the macro- and micronutrients from the 2 types of study bread were manually added to the dataset based on the type of bread and actual reported bread consumption. This final dataset was then exported into SPSS (version 29; IBM Corp) and was treated as continuous data.

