### Blinding and Allocation Concealment

Participants were not informed of the bread ingredients until the completion of the study data collection to maintain blinding. Analysts and researchers were blinded to the order of treatment that the participants received and to which group the participants were assigned during data collection and remained blinded until the statistical analysis of the primary outcome data was completed. The manufacturer of the bread was responsible for labeling both breads to maintain blinding of research team members. To further increase blinding, the manufacturer added colored malt to the placebo bread to make both breads visibly indistinguishable. Specified research team members were responsible for the randomization, enrollment, and data collection of participants; the handout of the intervention and placebo bread; and the management of the stock. Unblinding was only permissible once statistical analysis of the primary outcome data was completed.

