#### Statistical Analysis Plan

This study was conducted as a superiority trial. The guidelines of the Committee for Proprietary Medicinal Products (now termed Committee for Medicinal Products for Human Use) require intention-to-treat analysis [93]. For a crossover design, the intention-to-treat analysis means that every enrolled participant who has consumed both the intervention and placebo bread is included despite dropout or noncompliance. All data from randomized participants who received at least one intervention dose and had at least one postintervention measurement will be analyzed.

The mean differences from the baseline of most outcomes will be compared between groups and referred to as a between-group comparison. For most outcomes, within-group analysis (after the intervention compared with baseline) will also be performed. For metabolome analyses, postintervention values (not the mean differences) will be compared within and between groups.

All statistical analyses will be performed using SPSS statistics (version 29; IBM Corp) or R (version 4.3.1) by blinded researchers under the guidance of an independent biostatistician.

Baseline characteristics will be presented using descriptive statistics. The mean and SD, or median and range, will be used to describe continuous variables. Frequencies or percentages will be used to describe categorical variables. The group effects (ie, the mean change from baseline between groups) will be assessed using (parametric) 2-tailed *t* tests and (nonparametric) Mann-Whitney or Kruskal-Wallis tests for symmetrically and asymmetrically distributed data. Categorical variables will be assessed using chi-square tests (or Fisher exact tests for small samples). A 2-tailed *P*<.05 is determined as statistically significant. A value of *P*≤.10 will be considered a trend for most variables except for the microbiome data.

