#### Data Quality and Assurance

The researchers collecting data were trained accordingly in data collection, maintaining security and health-related confidentiality.

Due to the large amount of data to be collected, there may be an inherent risk of errors during the data entry into the data bank. All paper-based data were handled by blinded study personnel, and participants were strongly encouraged to enter survey data directly into the database via email links to the surveys and via the app to minimize this risk.

The nutrition graduates who entered the raw food and beverage diary data maintained a data entry assumption spreadsheet to ensure consistency of data entry. The study dietitian will independently audit 20% of the food diaries entered into the dietary analysis program (Foodworks Online; version 1.0) by the nutrition graduates. Diaries were checked for accuracy, consistency, and completeness. Extreme values or outliers for specific nutrients were identified and clarified by reviewing the assumption spreadsheet and raw food and beverage diary data.

A formal data monitoring committee was not required as the intervention and placebo breads in this study are considered as sufficiently low risk that no harm is anticipated to occur beyond the risks of standard care and everyday life.

Data monitoring occurred through weekly meetings of the research team. The unblinded research team maintained concealment.

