#### Data Collection and Storage by Researchers

Data collection for questionnaires occurred electronically via the REDCap system using the unique identifier allocated to the participants at the point of consent to the study. Participants who preferred paper data collection were accommodated. Paper-based and telephone-collected data were entered directly into electronic data collection systems (using REDCap) as soon as they were received.

Biological and physiome data were analyzed as per the aforementioned measures. The data files were stored in Microsoft Excel (Microsoft Corp) for raw data and as data analysis files (SPSS statistics version 29.0 or R statistical software version 4.3.1). These data were only identified by the unique code of each participant. Participants were identifiable to researchers only by their study code. Biological samples were stored in secure facilities with restricted access until publication of the results but not longer than 10 years, after which they will be destroyed hygienically in accordance with New Zealand Standard 4304:2002 (management of health care waste) or with the appropriate *karakia* (for Māori participants).

Raw data collected in hard copy were stored after electronic data entry as part of the case report form in a locked filing cabinet. All electronic data files generated in the study were stored on a password-secured University of Otago server or Otago OneDrive cloud storage and were accessed (and downloaded as needed) via the password-protected computers of named investigators and stored on locked premises. A master file containing participants’ personal identifying information was only accessible to the researchers involved in data collection. The blinded researchers had only access to deidentified raw data files and were responsible for the final data analysis.

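### Blinded analysis is claimed for all outcomes, but the unblinding rule secures it only for the primary composite

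*Protocol article*

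**What the plan says.** Two sections of the protocol article make a general claim of blinded analysis. The Statistical Analysis Plan section states: "All statistical analyses will be performed using SPSS statistics (version 29; IBM Corp) or R (version 4.3.1) by blinded researchers". The section on data collection and storage adds: "The blinded researchers had only access to deidentified raw data files and were responsible for the final data analysis".

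Two other sections set or report an earlier end to blinding. Blinding and Allocation Concealment says that analysts and researchers "remained blinded until the statistical analysis of the primary outcome data was completed", and gives the rule: "Unblinding was only permissible once statistical analysis of the primary outcome data was completed". It sets no condition for any other outcome. Dietary Intake, written in the past tense, gives the timing of its last data step as "After the primary outcome was analyzed and the study was unblinded to the intervention". In that step, nutrient values for the study breads were entered by hand, according to which bread was eaten and how much of it was reported. Only then was the dietary dataset final. That dataset carries fiber intake, the third of the seven secondary aims under Hypotheses and Objectives.

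On staff, Data Quality and Assurance says: "The unblinded research team maintained concealment". No section says who this team was. The blinding section says that the manufacturer labeled the breads so that the research team would stay blind, and that researchers were blind while data were collected.

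**The concern.** A reader of the Statistical Analysis Plan section will credit blinded analysis to every result of the trial. The unblinding rule supports that for one result only.

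This matters because the secondary analyses leave some decisions to the analyst. The choice between a t test and a rank test depends on a judgement about symmetry. Metabolite differences are to be tested by t test or Wilcoxon rank sum test. The most discriminating metabolite features are picked for the PLS-DA models. A trend label at P≤.10 applies to most variables, which makes a borderline result easier to report. Blinding the analyst is the usual guard against such decisions being swayed by the result they produce. If the guard stops at the primary outcome, the article should say so.

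**Working it through.** No arithmetic applies. The check sets the statements side by side and asks whether they can all be true.

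1. **Who analyses?** Statistical Analysis Plan: blinded researchers, for all analyses. Data storage section: blinded researchers, for the final analysis.
2. **Until when are they blind?** Blinding section: until the primary outcome analysis is complete. The limit is placed on analysts and researchers themselves, so the conflict is not removed by supposing that only a dispenser or data manager learns the code.
3. **Was the code broken?** Dietary Intake reports that it was, after the primary analysis and before the dietary dataset was complete. At least one secondary outcome, fiber intake, was therefore not ready for analysis when the study was unblinded.
4. **Was other work outstanding?** Results says that analysis of all outcomes was planned for completion by the last quarter of 2024, and the article is dated 29 August 2024. It does not say which secondary analyses were already done. Read with step 3, the study had been unblinded while some analysis was still to come.
5. **Does any statement keep analysts blind for a secondary comparison after that point?** Only the general claims in step 1, which steps 2 and 3 contradict.
6. **What is described as blind regardless?** Participants were not told the bread ingredients until data collection ended, and they entered the questionnaires, bowel diary and dye sightings themselves. Paper data were handled by blinded personnel. Capsule data from the 15-person subset were blinded when the capsule company's team read them. For these measures the exposed step is the later statistical comparison, not the measurement.
7. **Who was the unblinded team?** The blinding section gives randomization, enrollment, data collection, bread handout and stock control to specified team members. If the unblinded team was drawn from them, it may include people who collected outcome data. The article does not settle this.

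The statements in steps 1 and 2 cannot both hold for secondary outcomes. What the text secures is a blinded analysis of the composite.

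**The case against.** The strongest reply is that the unblinding rule sets an earliest time and does not order every analyst to be unblinded. Dietary Intake describes one use of the code, and that use was unavoidable: study-bread nutrients cannot be added without knowing the bread. On this view the analysts of gut comfort, lipids, metabolites and transit time may have stayed blind, as the Statistical Analysis Plan section says. This stands as a limit on the point. It does not remove the contradiction, because the blinding section ends the blinding of the analysts themselves, and one merge step does not require unblinding those who analyse other outcomes.

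A second reply is that the room for bias is small. The test choice is tied to the distribution. Metabolite features are chosen by an importance score with permutation and cross-validation checks, and PLS-DA selects the same features whether the classes are called A and B or named by bread. This largely stands. Some discretion remains, but nothing shows that it would favor the fortified bread.

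A third reply is that the unblinded team may simply be staff who handled the bread. That is possible. The mention shows an undefined role that fits poorly with the blinding section; it does not show unblinded analysis.

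A reader might infer that all seven groups of secondary aims were analysed with the bread known, or that the diary outlier checks were. The documents support neither. They permit unblinded secondary analysis without reporting it, and they do not date the diary checks relative to unblinding, while stating that paper data were handled by blinded personnel.

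**Conclusion.** The point holds as a contradiction about who was blind and for how long. Blinded analysis is claimed for all outcomes and secured for one, the primary composite. For secondary outcomes the statistical comparison may be made with the bread known. Data capture and capsule read-out are stated to be blinded, and the primary analysis is not affected.

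The size of any bias cannot be derived from the document. The conclusion rests on taking the blinding section at its word, that the limit applies to analysts, and on taking the past tense in Dietary Intake as a report of what happened. It deserves correction because a stated property of the trial is not delivered by its own unblinding rule. It does not threaten the main result.

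**What to change.** - For secondary analyses not yet run, have someone outside the analysis merge the bread nutrients and issue the datasets under coded A/B labels to analysts who have not seen the allocation. Release the code to them only when those analyses are locked.
- Limit the claims in the Statistical Analysis Plan and data storage sections to the analyses actually done blind, and mark the others as unblinded in the reports.
- Reconcile the blinding section with Data Quality and Assurance: say who the unblinded team was, when they learned the code, and whether they collected outcome data.

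The cost is a recoding step, possibly a different analyst, and a wording correction. There are two limits. New labels cannot re-mask anyone who already knows the allocation; where no unexposed analyst is available, disclosure is all that remains. Fiber intake cannot be fully masked, because the merged values reveal the bread.
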